## Abstract

**Background:**

Low mood is a common mental health problem affecting up to 121 million people worldwide and is common in students, particularly international students. Cognitive behavioural therapy (CBT) is known to be effective as a treatment for low mood and anxiety when delivered one to one by an expert practitioner, however this can be expensive and many services have waiting lists and delayed access. A range of additional ways of increasing access to services includes the offer of online courses such as computerised CBT as a possible additional pathway for care. This project aims to test the feasibility of a pilot randomised controlled trial of an online CBT-based life skills course with Chinese-speaking international students experiencing low mood and anxiety.

**Methods/design:**

Chinese-speaking international students with symptoms of low mood and/or anxiety will be recruited from the University of Glasgow, Scotland. Participants will be remotely randomised to receive either immediate access (IA) or delayed access (DA) to a guided/supported online CBT-based life skills package, the “Living Life” package (Chinese version). Participants will be randomly assigned to IA or DA to the intervention. The primary end point will be at 3 months when the delayed group will be offered the intervention. Levels of depression, anxiety, social functioning and satisfaction will be assessed.

**Discussion:**

This pilot study will test the trial design, ability to recruit, gather completed questionnaires, test drop-out rates and investigate completion and acceptability of the package. The study aims to reduce uncertainties about the delivery of a future substantive study and will also inform a sample size calculation for that subsequent substantive randomised controlled trial (RCT) which will be carried out to determine the effectiveness of the online package in improving low mood and anxiety in the Chinese-speaking student population.

**Trial registration:**

Current Controlled Trials ISRCTN30816908

## Background

An increasing number of international students who speak Chinese choose to study overseas, including in Scotland. These students face many challenges such as adjusting to the foreign educational, social, economic, interpersonal and political environment. They can also experience significant fresh challenges to world views such as different perceptions of democracy, freedom, openness, equality, liberty and individualism.

International university students experience a high degree of stress and distress and encounter various types of challenges and problems [1–3]. According to findings from the Mental Health Foundation, nearly one-fifth of adults living in the UK experience anxiety or depression. Depression amongst international students has been found to be up to 60 % higher than in host nation students [4]. Problems such as symptoms of depression are common and can affect students’ development and growth during their time studying overseas. Treatments for depression and anxiety include antidepressants and talking therapies. NICE [5] reviewed the evidence base for talking therapies and recommends the use of self-help resources based on a cognitive behavioural therapy (CBT) model for low mood, anxiety and depression. However, access to evidence-based psychological/talking therapies can be difficult, due to a significantly larger demand than supply and also the reluctance by some to access help for mental health difficulties [5]. Problems with accessing services and a scarcity and inequitable geographic distribution of accredited therapists all contribute to long waiting times for therapy [6]. In addition, international students also have little access to CBT in their native language and which takes into account their background and culture. More widely in the NHS, NICE recommends that access to CBT can also be provided using so-called low-intensity approaches such as CBT-based books and also delivery via computerised CBT (cCBT). CBT resources are recommended for the treatment of depression and anxiety in patients who have mild to moderate mental health problems.

The effectiveness of cCBT resources for use in Chinese-speaking populations has only been investigated to a limited extent. Choi et al. [7] supported the efficacy and acceptability of a computerised cognitive behavioural therapy (cCBT) program in reducing symptoms of depression in Chinese Australian adults (not students). In this study, the Chinese depression cCBT program, “Brighten Your Mood”, consisting of an 8-week program with six CBT online educational lessons, homework assignments, Chinese or English additional resources and weekly telephone support, was adopted to treat Chinese Australians with depression. Fifty-five Chinese Australians experiencing depression were randomly allocated to either an immediate treatment group or to a delayed access control group. After treatment, immediate access group participants reported significantly reduced symptoms of depression on the Chinese versions of the Beck Depression Inventory (CBDI) and Patient Health Questionnaire-9 item (CB-PHQ-9); when compared to the control group. Participants also rated the online treatment procedure as acceptable, and improvements were maintained at the 3-month follow-up. Furthermore, Kwok et al. [8] carried out a study investigating the effectiveness of an online CBT package for family caregivers of people with dementia. Thirty-six carers participated in a 9-week online CBT course. Based on the pre- and post-test on the Chinese version of the Neuropsychiatric Inventory Questionnaire and two domains of the Revised Scale for Care-giving Self-Efficacy, a statistically significant reduction in family caregivers’ distress was evident following the intervention.

Previous work on the need to culturally adapt CBT treatments for Chinese-speaking populations has been done. Ying et al. [9] explored how depression is conceptualised by Chinese American college students and considered the differences between Chinese and American perspectives on illness. Whereas American culture takes a dualist approach, where mind and body are viewed as separate entities; the mind, body and the social context are all integrated with each other within the Chinese medical model. They found that students with greater experience of living in a western culture seem to start to conceptualise depression in a very similar way as the host nation. They attributed this to the increased cross-cultural contact experienced by the student group.

However, no studies to date have used computerised CBT that has been culturally adapted for Chinese-speaking international students. Such packages might provide an effective intervention for students facing low mood and anxiety. Gellatly et al. [10] have suggested that the offer of such resources is more effective when guidance/support is provided.

### The student life skills training intervention

The study will test the delivery of an educational life skills package, “Living Life (LL)–Chinese version”, with the option of Mandarin and Cantonese Chinese language resources. The course teaches key life skills and is based on an existing CBT model with a strong educational focus. The content has been evaluated as a series of face-to-face classes [11, 12]. The free-access English language website is widely used with just under 30 million hits a year. The pilot trial aims to clarify many areas of uncertainty of the Chinese version of the Living Life course that would need to be addressed before moving to a future larger substantive study; for example, the ability to—recruit Chinese-speaking international students, deliver the Chinese version course and support the course and gather baseline and follow-up data of anxiety and depressive symptoms.

### Aims

The aim of this study is to recruit Chinese-speaking international students based in the West of Scotland and experiencing symptoms of depression and/or anxiety. We will include both those diagnosed with depression as well as those with raised mood scores without a formal diagnosis.

In this pilot study, the main aim will be to investigate take-up, drop-out and completion rates of the online course and the completion rates for data collection.

Secondary outcomes will be mood ratings at 3 months. We will use changes in the Patient Health Questionnaire 9 (PHQ-9) [13] score to provide data relating to the effect of the intervention on depression levels. The PHQ-9 is our chosen primary outcome measure for the future substantive RCT and provides a valid and reliable measure of depression. It will provide an indication of efficacy and, together with the drop-out/retention rate, will be used to provide a power calculation for the future larger RCT; providing evidence that a change in depression levels between the intervention and control groups can be observed. This is an unfunded PhD study to establish viability of applying for a substantive later funded RCT.

The specific research questions of the study are outlined below.

### Research questions

Primary question:Is the study design feasible—is it possible to recruit Chinese-speaking international students from a University setting, randomise participants and collect data at baseline, 3 months and 6 months?

Secondary questionsb.To what extent will participants adhere to the online intervention?c.Is the Living Life package acceptable to Chinese-speaking students?d.How many participants will be needed for a sufficiently powered future RCT?

By gathering information about uptake, retention, ability to gather data, as well as obtaining an estimate of treatment effect, it will be possible to complete a power calculation to estimate the sample size required for the future substantive study.

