## Methods/design

### Overview

This is a pilot study with a randomised controlled design. This study will investigate the possibility of delivering the culturally adapted Living Life online life skills resource to Chinese-speaking international students. In this RCT, 50 % of participants will be randomly allocated to receive immediate access (IA) to the Living Life (LL) online intervention and 50 % will be in the delayed access control group (DA). The primary end point is 3 months at which point the control arm will be invited to begin the intervention. A further follow-up point will be at 6 months post-randomisation. This 6-month time point was chosen as a comparative, reasonable follow-up length to fit the structure of the academic year.

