### Participants

The aim is to recruit up to 50 participants in total to provide an indication of the take-up, use and impact of the course on low mood or anxiety; and identify any problems with recruitment, delivery of the intervention and completion of evaluation measures. Such problems could be recruitment difficulties, drop-out during the intervention, poor adherence to the online course and failure to complete follow-up measures.

Inclusion criteria:

To enter the study, individuals must be Chinese-speaking (Mandarin or Cantonese) international students aged 18 years of age or more, registered as students (undergraduate or postgraduate) at the University of Glasgow and living in the UK for the next 2 months. This is to ensure they are in the UK when using the intervention so that appropriate support can be offered in the event of identified risk. Current symptoms of depression with the score 5+ on the PHQ-9 [13] depression questionnaire and/or a score of 5+ on the generalised anxiety disorder −7 (GAD-7) [14] scale (Chinese language versions) must be present for eligibility. Participants will be required to have broadband web access and also be willing and able to use the online course.

Exclusion criteria:

Participants will be excluded if they do not fulfil the inclusion criteria or are currently receiving specialist mental health treatment or current psychotherapy/counselling. Students who are on antidepressants will not be excluded, but we will record the drug, dose and length of time on the medication.

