### Statistical analyses

Analysis will be descriptive statistics, *t*-tests comparing means, chi square analysis of frequency data and ANOVA analyses. Evaluable data and intention to treat analysis will occur. Results will be analysed and interpreted using SPSS. The majority of the results will be simple descriptive data summarising take-up, completion and drop-out rates. Finally, the PHQ-9 data will be used to perform a power calculation for the future large RCT.

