### Knowledge added to the literature

In the pilot study, the sample sizes are chosen to provide the information required. They are deliberately not informed by a power calculation as the purpose of this study is to provide the information required to test delivery of the components of the study and to provide a power calculation for a future substantive study. Moreover, the primary outcome will be the take-up, drop-out and completion rates of the online course and the collection rates for data. Secondary outcomes will be mood rating scales using descriptive statistics. We will use changes in PHQ-9 score to provide an impact of effect of the intervention on mood at 3 months, which will be the primary outcome for the future substantive RCT.

In addition, the results of the current study relating to changes in PHQ-9 and GAD-7 scores could inform and guide practitioners about the mental health needs of Chinese international students and the difficulties faced when they study overseas [3].

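### The future RCT's power calculation is to use the treatment effect observed in a pilot of at most 50, which is too imprecise for that purpose or for showing a between-group change

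*Protocol article*

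**What the plan says.** The Research questions section asks, as secondary question (d), how many participants a sufficiently powered RCT would need. It lists uptake, retention and the ability to gather data as inputs, and then adds the effect: "obtaining an estimate of treatment effect, it will be possible to complete a power calculation to estimate the sample size required".

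The Aims section says of the PHQ-9 change: "It will provide an indication of efficacy and, together with the drop-out/retention rate, will be used to provide a power calculation". The same sentence goes on to promise more: "providing evidence that a change in depression levels between the intervention and control groups can be observed".

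Statistical analyses says only that "the PHQ-9 data will be used to perform a power calculation for the future large RCT", without saying which feature of those data.

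On size, the Participants section says "The aim is to recruit up to 50 participants in total", and the Overview gives equal allocation. The Discussion (Knowledge added to the literature) says that "the sample sizes are chosen to provide the information required", and that this size deliberately does not come from a power calculation.

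The article does not name a clinically important PHQ-9 difference or an external effect estimate for the future trial. It also does not restrict the pilot's contribution to the SD and retention.

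**The concern.** A pilot need not be powered, and it is a sound source for retention, adherence and the outcome SD. The observed treatment effect is a different kind of input. Required sample size varies with the inverse square of the effect, so sampling error in a small pilot is greatly magnified in the main-trial figure. A chance-large estimate gives an underpowered main trial, a chance-small one gives an unnecessarily large trial, and a zero or reversed one gives no figure at all.

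The statement that the pilot will show an observable between-group change has the same weakness. With about 25 per arm, failure to see a difference would be a common result even if the intervention works. Question (d) is a stated deliverable of the study, so the method given for answering it matters.

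**Working it through.** **Inputs from the article.** At most 50 participants, allocated 1:1, so n = 25 per arm before attrition. The future primary outcome is PHQ-9 at 3 months. The article gives no alpha, power, effect size, SD or attrition rate, so it has no figure to reproduce.

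**Assumptions, not in the article.** Two-sided 5% level and 80% power; true standardised difference d between 0.3 and 0.8; PHQ-9 SD of 4 to 6 points; full retention, with 20% loss (20 per arm) as a variant. The observed effect is taken at face value as the target difference.

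**1. Precision of the pilot effect.** Half-width of the 95% CI in SD units = t(0.975; 2n−2) × √(2/n).
- n = 25: 2.011 × √0.08 = 0.57 SD, which is 2.3, 2.8 or 3.4 PHQ-9 points for an SD of 4, 5 or 6.
- n = 20: 2.024 × √0.10 = 0.64 SD.

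**2. What one observed value would imply.** Take an observed d of 0.4 with n = 25. SE = √(2/n + d²/(4n)) = √(0.08 + 0.0016) = 0.286, so the 95% CI is about −0.16 to 0.96. Main-trial size per arm = 2(1.96 + 0.84)²/d² ≈ 15.7/d². This gives 99 at the point estimate, 18 at the upper limit and no value at the lower limit.

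**3. How often the resulting size is far out.** Because N varies as 1/d², N falls below half the needed figure when the observed d exceeds √2 times the true d. It exceeds double, or does not exist, when the observed d is below the true d divided by √2. Noncentral t probabilities for n = 25, in agreement with simulation:

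| True d | Needed per arm | Pilot power | N below half | N above double, or none | Either |
|---|---|---|---|---|---|
| 0.3 | 175 | 18% | 33% | 38% | 71% |
| 0.4 | 99 | 28% | 29% | 34% | 62% |
| 0.5 | 63 | 41% | 24% | 30% | 54% |
| 0.8 | 25 | 79% | 14% | 21% | 35% |

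At true d = 0.4 the interquartile range of the computed size is about 44 to 358 per arm, and 28% of pilots lead to a main trial with true power below 50%. The observed effect is zero or reversed in about 14%, 8% and 4% of pilots at d = 0.3, 0.4 and 0.5.

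With 20% loss, the interquartile range at d = 0.4 is about 40 to 449 per arm, and 10% of pilots show a zero or reversed effect.

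**4. Contrast with the SD.** With 48 degrees of freedom the 95% CI for the SD is 0.83 to 1.25 times its estimate. N varies as SD², so it moves only by a factor of 0.70 to 1.56. The pilot can therefore support this input, with some allowance for imprecision.

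**5. Baseline adjustment.** An assumed baseline-to-follow-up correlation of 0.5 multiplies the half-width by √(1 − 0.25) = 0.87, giving 0.57 × 0.87 = 0.49 SD. This helps only modestly.

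**The case against.** The strongest reply is that this is a feasibility study. Its primary question and primary outcome concern recruitment, take-up, drop-out and data completeness, and mood scores are secondary and descriptive. The main trial will be sized later, in another protocol and a grant application. The article does not say that the point estimate will be used without its interval or without clinical judgement, so the figures above model the plainest reading. This stands as a limit on severity. It does not remove the point, because the article names the effect estimate as an input and offers nothing else as the target difference.

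A second reply is that the true effect may be larger. The Background describes a trial of online CBT in 55 Chinese Australian adults with a significant benefit. An unadjusted t-test at that size needs an observed d of about 0.54. At d = 0.8 the problem is clearly smaller: with 20 per arm the interquartile range is about 15 to 46 against 25 needed. That is fair, but one small significant trial may overstate the effect, and even at 0.8 with full retention about a third of pilots would be out by a factor of two.

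Third, Statistical analyses taken alone fits using the SD only. That is correct, so the passage needs clarifying rather than correcting. The Discussion's remark on sample size likewise does not claim that 50 participants estimate an effect precisely.

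Two stronger readings are tempting. A reader might infer that a disappointing pilot effect would lead to the main trial being wrongly abandoned. The article links the pilot to the viability of applying for funding but states no effect-based go/no-go rule, so this is not supported. A reader might also note that about half of trials sized this way would have true power below 80%. That holds for a roughly median-unbiased estimate from a pilot of any size, and so says nothing about this one.

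**Conclusion.** The point holds for the two uses stated in Aims and Research questions: the observed effect as an input to the main-trial power calculation, and the pilot as evidence of an observable between-group change. About 25 per arm before attrition is too few for either. Across true effects of 0.3 to 0.5, more than half of pilots used this way would put the main-trial size out by a factor of two or more, or give no size. That result rests on the assumed level, power, full retention and face-value use of the estimate. Attrition makes it worse, and a large true effect makes it milder.

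Mis-sizing is probable under these assumptions, not certain. This should be fixed but is not critical: the pilot's conduct, data and primary feasibility outcome are untouched, and the same data can serve a better sizing method.

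**What to change.** In Aims and Research questions, state that the future RCT will be sized on a prespecified clinically important PHQ-9 difference. State that the pilot will supply the PHQ-9 SD (with an allowance for its imprecision), the baseline-to-3-month correlation and retention. Amend Statistical analyses to say that these are the PHQ-9 quantities that will be used. Report the pilot effect with its 95% CI only. Delete from Aims the clause "providing evidence that a change in depression levels between the intervention and control groups can be observed".

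Fixing the difference before the pilot data are seen is preferable; it must in any case be fixed before the main trial. For illustration only, with an SD of 5 and differences of 2, 2.5 or 3 points, the main trial would need 99, 63 or 44 per arm. Allowing for 20% attrition (dividing by 0.8), it would need 124, 79 or 55.

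The change is to wording only and needs no new data. Its one cost is a modestly larger main trial if a conservative SD is used. For example, the upper 80% confidence limit, one convention among several, is about 1.12 times the estimate with 38 degrees of freedom (20 per arm), which raises N by about 24%.

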## Methods/design

### Overview

This is a pilot study with a randomised controlled design. This study will investigate the possibility of delivering the culturally adapted Living Life online life skills resource to Chinese-speaking international students. In this RCT, 50 % of participants will be randomly allocated to receive immediate access (IA) to the Living Life (LL) online intervention and 50 % will be in the delayed access control group (DA). The primary end point is 3 months at which point the control arm will be invited to begin the intervention. A further follow-up point will be at 6 months post-randomisation. This 6-month time point was chosen as a comparative, reasonable follow-up length to fit the structure of the academic year.

### Participants

The aim is to recruit up to 50 participants in total to provide an indication of the take-up, use and impact of the course on low mood or anxiety; and identify any problems with recruitment, delivery of the intervention and completion of evaluation measures. Such problems could be recruitment difficulties, drop-out during the intervention, poor adherence to the online course and failure to complete follow-up measures.

Inclusion criteria:

To enter the study, individuals must be Chinese-speaking (Mandarin or Cantonese) international students aged 18 years of age or more, registered as students (undergraduate or postgraduate) at the University of Glasgow and living in the UK for the next 2 months. This is to ensure they are in the UK when using the intervention so that appropriate support can be offered in the event of identified risk. Current symptoms of depression with the score 5+ on the PHQ-9 [13] depression questionnaire and/or a score of 5+ on the generalised anxiety disorder −7 (GAD-7) [14] scale (Chinese language versions) must be present for eligibility. Participants will be required to have broadband web access and also be willing and able to use the online course.

Exclusion criteria:

Participants will be excluded if they do not fulfil the inclusion criteria or are currently receiving specialist mental health treatment or current psychotherapy/counselling. Students who are on antidepressants will not be excluded, but we will record the drug, dose and length of time on the medication.

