### Immediate access (IA) group

Participants randomised to IA will be given log in details for the LL online intervention and will begin receiving weekly support via automated emails in either Mandarin or Cantonese. In addition, personalised short weekly support sessions will be offered by email from a Chinese-speaking counsellor. Support will focus on encouraging module completion and practicing what has been learned. Copies of emails will be retained to check adherence to the Plan, Do, Review model [15] of support. This model uses two worksheets (planner and review sheets) to apply what is learned in practice.

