### Delayed access control (DA) group

Participants randomly allocated to the delayed access group will be informed that they will be given access to the online course after a delay of 3 months. As in the IA group, all participants will continue with any usual treatment as required.

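### The 2-month UK-residence criterion ends at least a month before the delayed arm can start the intervention, so for that arm it does not secure what it is meant to secure

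*Protocol article*

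**What the plan says.** The inclusion criteria in the Participants section apply to everyone entering the study ("To enter the study, individuals must be Chinese-speaking (Mandarin or Cantonese) international students"). They set the residence requirement and give its purpose together: "living in the UK for the next 2 months. This is to ensure they are in the UK when using the intervention" and, following from that, "so that appropriate support can be offered in the event of identified risk".

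The two arms start the course at different times. Under the immediate access heading, "Participants randomised to IA will be given log in details for the LL online intervention" after randomisation. The delayed access section tells control participants that "they will be given access to the online course after a delay of 3 months". The Overview agrees: "The primary end point is 3 months at which point the control arm will be invited to begin the intervention". The last follow-up is at 6 months after randomisation.

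The article gives no separate residence period for the delayed arm, no extension of the 2 months, and no check of residence at month 3.

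**The concern.** The sponsor presents the residence rule as a risk safeguard: it ties support to the participant being in the UK during use. For half of the randomised participants, use cannot begin until the period covered by the rule has ended. A student who plans to leave the UK after two months meets the criterion, can be allocated to delayed access, and may open the course for the first time abroad.

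What is at stake is mainly safety. Most of the urgent-help sources listed under Risk management (GP, NHS24, student counselling, A+E) are UK services. Interpretation is a lesser matter. Take-up of the course is part of the pilot's primary outcome, and without knowing where delayed-arm participants are at month 3, a reader cannot tell whether low take-up in that arm reflects the package or the participants' circumstances.

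**Working it through.** The protocol has no figure to reproduce here. The check is a comparison of timelines.

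**Inputs**
- Residence window: 2 months from entry (Participants).
- Start of use, immediate arm: month 0, on randomisation (Immediate access group).
- Start of use, delayed arm: month 3 (Overview; Delayed access control group).
- Last follow-up: month 6 (Overview).
- Sample: up to 50, allocated 50% to each arm (Participants; Overview).
- Package: eight modules, with no completion time stated (Intervention). One module per week is my assumption, used only where marked.

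**Delayed arm**
- Overlap of residence window and use = max(0, 2 − 3) = 0 months.
- Gap between end of window and start of use = 3 − 2 = 1 month. If randomisation follows entry with a lag, the gap is longer, because the 2 months run from entry. One month is therefore a minimum.
- Participants concerned = 0.5 × 50 = 25 at most.
- None of these results depends on how fast the modules are worked.
- At one module per week (assumption), 8 weeks × 7 / 30.4 ≈ 1.8 months, so use would run from month 3 to about month 4.8. If use continued to the last follow-up, it would run from month 3 to month 6.

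**Immediate arm**
- At one module per week (assumption), use runs from month 0 to about month 1.8, inside the 2-month window. Only slower use would run past it.

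**Could the 2 months be counted from first log-in?** No. The requirement is a condition of entry, assessed before randomisation, when allocation is not yet known. It looks forward from that point.

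**Calendar (Trial status)**
- Recruitment begins in October 2014 and final outcome data come in May/June 2015. The first delayed-arm access is then about January 2015 (October + 3 months). If the final data are the last participants' 6-month data, the last access opens in about February/March 2015 (May/June − 3 months).

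**The case against.** The strongest reply is that a lapsed criterion does not put anyone abroad. Entrants must be registered at the University, the 6-month follow-up was chosen to fit the academic year, and the calendar above places delayed-arm use roughly between January and May/June. Presence in the UK is likely for many. The Risk management section also assigns every participant a Chinese-speaking support worker who makes weekly contact and reports deterioration to the clinical lead. Support is delivered by email, so it can continue abroad. The article also mentions risk management protocols. All of this stands, and it limits the practical consequence. It does not close the gap: the sponsor stated that UK presence during use was needed for appropriate support, and the entry rule does not ensure it for this arm.

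A reader might infer three stronger points that the documents do not support.

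- **Differential loss or biased retention.** The criterion is applied identically before randomisation, so departures after month 2 should be similar in the two arms. The package and the measures are online, so leaving the UK does not in itself cause non-use or missing questionnaires.
- **The rule also fails the immediate arm.** At the assumed weekly pace the eight modules fit inside the 2 months, and the article does not say how long that arm keeps access.
- **A shortfall of about 3 months.** That figure (about 5 − 2) depends on the assumed pace. The documents themselves give only the gap of at least 1 month and the zero overlap.

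**Conclusion.** The point holds as an internal inconsistency between the residence criterion, with its stated purpose, and the delayed-access schedule. The window closes at least 1 month before the delayed arm can begin and covers 0 months of its use, for about 25 of up to 50 participants. This rests only on the article's own 2 and 3 months, with the 2 months read as running from entry, as the text requires.

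The documents give no number of students expected to leave the UK, so the size of the resulting risk is unknown. It should not be read as a claim that delayed-arm participants will be abroad. The between-arm comparison at 3 months is complete before delayed access opens, and the sample size does not depend on this rule; neither is affected.

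**What to change.** Reconcile the Participants, Overview and Delayed access control sections by one of two routes.

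1. Word the residence condition so that it matches the period in which a participant may use the package under either allocation, since allocation is unknown at screening.
2. Keep the entry condition, and ask and record UK residence when delayed access opens at month 3. The sponsor's risk-support arrangements can then be applied with that information, and delayed-arm take-up can be read alongside it.

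Under the second route, whether access depends on the answer is for the sponsor to decide. Withholding it would conflict with what delayed-arm participants are told about receiving access, so that text would need to be reconciled too.

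The cost is one extra question at month 3, or, if the window is lengthened, slightly narrower eligibility in a pilot whose primary question includes whether recruitment is possible.
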